#### Trial health questionnaire

The Trial Health Questionnaire includes questions on the participant’s employment status, social activities (e.g., smoking, alcohol use), pain assessment (Numeric Pain Rating Scale) and two surveys, the EQ-5D-5L [16] and the Reintegration to Normal Living Index (RNLI) [17].

The NPRS is a numeric version of the visual analog scale, with 0 representing no pain and 10 representing the worst pain the participants can imagine. Participants will be asked to indicate their pain on movement (deep breathing or mobilization). The EQ-5D-5L has been validated for a number of chronic conditions, including cardiovascular and respiratory disease. The EQ-5D-5L is comprised of a descriptive system as well as a visual analog scale that assesses dimensions related to mobility, self-care, usual activities, pain/discomfort, and anxiety/depression. Respondents are asked to report their health states by rating each dimension as one of five levels (no problems, slight problems, moderate problems, severe problems and extreme problems). The RNLI is a self-report questionnaire used to evaluate global function status of a patient during rehabilitation which was developed to qualitatively assess the ability of individuals with traumatic or incapacitating illnesses to reintegrate into normal life. The RNLI is a questionnaire that is comprised of 11 questions that assesses mobility, self-care, daily activity, recreational activity, and family roles. Reintegration to normal living was defined as the reorganization of physical, psychological, and social characteristics of an individual into a harmonious whole so that one can resume well-adjusted living after incapacitating illness or trauma [18]. Each domain contains a visual analogue scale. On one end: “does not describe my situation” (1 or minimal integration) and “fully describes my situation” (10 or complete integration). Individual item scores are summed to provide the total score. The higher the score, the better the patients perceived integration.

#### Study diary

The Study Diary is designed to provide a space for participants to record any adverse events they may have, healthcare resources they may use (e.g., emergency room visits, hospitalizations, doctors and specialist visits, test, procedures or surgeries) and to record any pain medications they were prescribed and taking. At each visit the trial coordinator will review the Study Diary with the participant and ask any additional supplemental questions to clarify information recorded in the Study Diary.

### Plans to promote participant retention and complete follow-up

Participants will be informed that they are free to withdraw from the trial at any time, without fear of any negative repercussions. Investigators may also withdraw participants from the trial (e.g., to protect the participants’ safety). All trial withdrawals will be documented by date and reason for withdrawal. If the participant chooses to withdraw prior to randomization, their data will be excluded from the trial. If a participant chooses to withdraw after randomization, their data will be included, unless otherwise requested.

There is minimal anticipated loss to follow-up, as the majority of the interval data (3 weeks, 12 weeks, 6 months, 18 months, 1, 2, 3, 4 and 5 years) will be collected at the same time that the participant has their standard scheduled post-surgery follow-up visit in clinic. The availability of a trial coordinator will ensure that the Trial Health Questionnaire is completed at each of these follow-up clinic visits. If a participant misses a follow-up visit, it will be considered a deviation from the protocol, but the participant will remain in the trial and all attempts to contact the participant to conduct the visit over the telephone will be made, even if the visit occurs late. Major deviations from the protocol will be documented (e.g., the nature of the deviation and rationale for the deviation) and the REB will be notified as per requirements.

### Data management

At each trial site, data will be collected from source documents and entered into the electronic Case Report Forms (eCRFs) on REDCap. The eCRFs are the primary data collection instruments for the trial. REDCap is a secure web application developed to optimize data collection and management for research databases. REDCap will allow authorized data abstractors to enter trial data into eCRFs on a password-protected server hosted behind the SJHH firewall. Access to the trial database will be controlled by the database administrator (the trial coordinator at the Central Coordinating Centre) with overall access to the REDCap system granted by a SJHH Super-User. Each abstractor will be given individual credentials, allowing for entered content to be associated with the applicable abstractor, which will assist with auditing procedures in the future. REDCap allows for electronic prompts (e.g., range checks, valid values, missing data) on the eCRFs, which will minimize errors and omissions at the time of data entry, and a Data Resolution Workflow module where data queries can be added in response to standard data edit checks for discrepancies, consistency checks against data already stored in REDCap, and protocol deviations to ensure the integrity of the trial data.

Videotapes will be transferred from the Toronto, Florida, and France sites using the SFTP (SSH File Transfer Protocol), which ensures all data transmitted is encrypted in transit. The data will be received into a secure server in the Central Coordinating Centre’s DMZ (demilitarized zone). All videotapes will be stored on a secure server at the Research Institute of St. Joseph’s Healthcare Hamilton.

### Confidentiality

All records identifying the trial participant will be kept confidential and, to the extent permitted by the applicable laws and/or regulations, will not be made publicly available. Participant confidentiality will also be maintained in all analyses and presentations. At the time of enrolment, each participant will be assigned a unique trial participant identification (PID) number. Relevant personal health information (PHI) (e.g., first and last name, date of birth, telephone number, medical record number) will be recorded in a Trial Code List which will link the PHI to the PID. Information in the Trial Code List will be used to obtain and collect participant trial data from health records, determine age and to complete follow-up telephone assessments. The PID number will be recorded in the eCRF and no PHI from the Trial Code List will be entered in the eCRF. The Trial Code List and REDCap will be password protected and stored on the SJHH Research Institute’s secure server and will be protected in accordance with local data protection laws.

### Plans for collection, laboratory evaluation and storage of biological specimens for genetic or molecular analysis in this trial/future use

Not applicable as biological specimens will not be collected as part of this trial.

## Statistical methods

### Statistical methods for primary and secondary outcomes

Baseline characteristics of both treatment groups will be compared to ensure homogeneity in the patient population. Descriptive statistics will be reported by treatment group where categorical variables will be reported as counts (percentages) and continuous variables as mean (standard deviation) or as median (25^th^ percentile, 75th percentile). All analyses of primary and secondary outcomes will be carried out based on the intention-to-treat principle. Unadjusted comparisons of continuous outcome measures will be carried out using an independent t-test or the Wilcoxon rank-sum test if the assumptions of the t-test were violated. Unadjusted comparisons of categorical outcome measures will be computed using the chi-squared test, or the Fisher’s exact test if any of the expected values in the contingency table is less than 5, or McNemar’s test. For adjusted analyses, multivariable logistic regression analyses will be used for binary outcomes and multivariable linear regression for continuous outcomes. The results of comparisons between groups will be presented as mean differences for continuous outcomes and relative risks or odds ratios for binary outcomes, with corresponding 95% confidence intervals and associated p-values. ANOVA will be used for repeated measures. Survival will be compared using the Kaplan-Meier method and cox proportional hazard models. Survival curves will be compared using the Log-rank test. P-values will be reported to three decimal places with p-values less than 0.001 reported as p < 0.001. All analyses will be performed using SAS. Table 3 provides a summary of the variables, measures and methods of analysis.

**Table 3 pone.0261767.t003:** Variables, measures and methods of analysis.

Variable/Outcome	Hypothesis*	Outcome	Method of Analysis

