#### Secondary objectives

In Phase A of this trial, we will compare differences in short-term clinical outcomes, and HRQOL outcomes at weeks 3 and 7; and months 6 and 12, which coincide with the intervals of oncological surveillance. We will also compute resource utilization and calculate the incremental cost effectiveness between RTS-Lobectomy and VATS-Lobectomy.

In Phase B of this trial, we will compare the difference in the 5-year survival data between the two arms. We will also compare differences in HRQOL outcomes at months 18 and 24; and years 3, 4, and 5, which coincide with the intervals of oncological surveillance. We will also compute resource utilization and calculate the incremental cost effectiveness between RTS-Lobectomy and VATS-Lobectomy.

RTS-Lobectomy is a new technology that has not been studied extensively yet against VATS-Lobectomy, so equipoise still exists. However, based on preliminary data from our experience and from literature, we hypothesize that for short-term clinical outcomes, RTS-Lobectomy leads to higher quality pathological staging by improved lymphadenectomy, and is associated with shorter duration of chest tube drainage; shorter hospital length of stay; less intraoperative blood loss; lower postoperative analgesia requirements; and less chronic postsurgical pain as compared to those who receive VATS-Lobectomy.

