### Trial design

The trial is an international, multi-centered, blinded, randomized controlled trial. Patients will be randomized to RTS-Lobectomy versus VATS-Lobectomy at a 1:1 allocation ratio (Fig 1).

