## Assignment of interventions: Allocation

### Sequence generation

A statistician who is a member of the Biostatistics Unit at St. Joseph’s Healthcare Hamilton, generated the randomization sequence using SAS [14]. Randomization was stratified by surgeon. For each surgeon, a unique randomization sequence using the random permuted-block design (with blocks of varying sizes) to randomize patients in a 1:1 ratio to one of two intervention arms, VATS-Lobectomy or RTS-Lobectomy, was generated. This method ensures that an approximately equal number of patients will be allocated to each treatment group.

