**SECONDARY**			
Short-Term Clinical Outcomes			
*Pathological Staging*	Improved	Pathological stage	McNemar’s test
*Lymph nodes*	More	Number of lymph nodes harvested	Independent t-test, Wilcoxon rank sum test/linear regression
*Duration of chest tube drainage*	Shorter	Number of days between surgery and chest tube removal	Kaplan-Meier method, Cox regression
*Hospital length of stay*	Shorter	Number of days between admission and discharge	Kaplan-Meier method, Cox regression
*Intra-operative blood loss*	Less	Volume of Intra-operative blood loss (mL)	Independent t-test/Wilcoxon rank sum test/ linear regression
*Post-operative analgesia requirements*	Less	In-hospital consumption (days, type, amount)	Independent t-test/Wilcoxon rank sum test/linear regression
*Chronic post-surgical pain*	Less	In-hospital pain (daily, scale)	Independent t-test/Wilcoxon rank sum test/ANOVA
Patient-reported Health-Related Quality of Life (HRQOL) outcomes	Improved	HRQOL scores, measured by the EQ-5D-5L at 3 and 7 weeks, and 6 and 18 months, and 1,2, 3, 4 and 5 years	Examine the distributions/ regression/ANOVA
Resource Utilization and Cost Effectiveness	More	Resource utilization tracking system, EQ-5D-5L, Return to Normal Living Index (RNLI), and employment status at 12 months	Incremental cost per quality-adjusted life year (QALY) gained will be calculated
Overall Survival	Improved	5-year survival difference	Kaplan-Meier method and cox proportional hazard models. Survival curves will be compared using the Log-rank test

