**SENSITIVITY**			
Patient-reported Health-Related Quality of Life (HRQOL) outcome	Improved	HRQOL scores, measured by the EQ-5D-5L at 12 weeks	Independent t-test/ linear regression with multiple imputation for missing data

*Expected that RTS-Lobectomy will improve or be more, less, fewer or shorter than VATS-Lobectomy for each variable/outcome.

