### Secondary analysis

Short-term clinical outcomes will involve aspects of perioperative care:
○ A higher quality of pathological staging is expected to occur with participants who have RTS-Lobectomy. Data on clinical and pathological staging will be compared.○ More lymph nodes are expected to be sampled for participants who have RTS-Lobectomy. The number of lymph nodes sampled for each patient will define the outcome measure.○ A shorter duration of chest tube drainage is expected to occur for participants who have RTS-Lobectomy. This will be measured by the number of days between the date of surgery and the date of chest tube removal.○ A shorter hospital length of stay is expected to occur for participants who have RTS-Lobectomy. This will be measured by the number of days between the date of hospital admission and the date of discharge.○ Less intraoperative blood loss (mL) is expected to occur for participants who have RTS-Lobectomy. This will be measured by the volume of blood loss in mL intraoperatively for each patient.○ Less post-operative analgesia requirements are expected to occur with participants who have RTS-Lobectomy. This will be measured by collecting the amount of analgesia consumed by each participant (e.g., type of medication used (e.g., PCA, epidural, intravenous, oral), the number of days the medication was used, and the amount used) in hospital.○ Less post-surgical pain is expected to occur in participants who have RTS-Lobectomy. This will be measured by collecting the pain score for each participant daily during their hospital admission.Resource Utilization and Cost Effectiveness

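### Pathological staging is assigned McNemar's test, a within-patient paired test that has no treatment arm in it and so cannot compare RTS with VATS

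*Protocol article*

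**What the plan says.** - **Hypothesis.** Secondary objectives, in the protocol article, expects that "RTS-Lobectomy leads to higher quality pathological staging by improved lymphadenectomy". The footnote to Table 3 applies the same direction to every row: "Expected that RTS-Lobectomy will improve or be more, less, fewer or shorter than VATS-Lobectomy for each variable/outcome". The staging hypothesis is therefore a contrast between arms.
- **Test assigned.** In Table 3, the Pathological Staging row has the hypothesis of improvement, pathological stage as the outcome, and a single method: "McNemar’s test". The lymph-node, blood-loss and analgesia rows each name a two-sample test and regression.
- **General text.** Under Statistical methods for primary and secondary outcomes, "Unadjusted comparisons of categorical outcome measures will be computed using the chi-squared test", then Fisher's exact test "if any of the expected values in the contingency table is less than 5, or McNemar’s test". No condition is given for when McNemar's test applies.
- **Data to be used.** Secondary analysis says of this outcome: "Data on clinical and pathological staging will be compared".
- **Design.** Trial design: "Patients will be randomized to RTS-Lobectomy versus VATS-Lobectomy at a 1:1 allocation ratio". Sequence generation describes permuted blocks within surgeon. Nothing matches an RTS patient to a VATS patient.

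**The concern.** McNemar's test is for two binary measurements on the same unit or on matched units. Between two independent arms it has no pairs to work on. The one pairing the text offers is clinical and pathological stage within a patient. Applied there, it tests whether moves up and moves down in stage are equally frequent, a statement about clinical staging accuracy that contains no treatment term.

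A significant result could be reported as improved staging with robotic surgery when the arms do not differ, and a real difference between arms could go unseen. The test also needs a binary variable. Eligible clinical stages run over I, II and IIIa, and the article gives no dichotomy.

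**Working it through.** **Sample size used below.** The plan gives no figure for staging, so the arm sizes come from Sample size. Phase A uses a difference of 0.07, SD 0.16, 80% power and a 0.05 level (taken as two-sided). The t-based calculation gives 82.98, so 83 per arm; 83 / 0.90 = 92.2, so 93 per arm and 186 in total. This reproduces the plan. Phase B has 296 per arm (592 in total).

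**The statistic.** With b patients upstaged and c downstaged, McNemar's chi-square is (b − c)² / (b + c) on 1 degree of freedom. Treatment arm does not appear.

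**Identical arms, unequal moves.** Assume 20% upstaged and 10% downstaged in both arms, 93 per arm.
- Pooled: b = 0.20 × 186 ≈ 37, c = 0.10 × 186 ≈ 19. (37 − 19)² / (37 + 19) = 324 / 56 = 5.79, p = 0.016.
- One arm alone: b ≈ 19, c ≈ 9. (19 − 9)² / 28 = 100 / 28 = 3.57, p about 0.06.
- With 19 up and 5 down of 93 in each arm, the exact McNemar p is 0.007 in each arm, while the between-arm chi-squared p is 1.0.

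**Different arms, balanced moves.** Assume 25% up and 25% down in RTS (23 and 23 of 93), and 10% up and 10% down in VATS (9 and 9 of 93). RTS restages 50% against 20%, or 2.5 times as many.
- McNemar: (23 − 23)² / 46 = 0 in RTS and (9 − 9)² / 18 = 0 in VATS.
- Between-arm chi-square on the proportion upstaged, 23/93 against 9/93: 186 × (23 × 84 − 9 × 70)² / (93 × 93 × 32 × 154) = 7.40, p about 0.007.

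**Simulation.** 4,000 trials per scenario, arms identical, exact McNemar at the 0.05 level. The table gives the percentage of trials rejecting. All rates are assumptions.

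| Up / down | n per arm | McNemar, RTS arm alone | McNemar, pooled | Between-arm chi-squared on upstaging |
|---|---|---|---|---|
| 10% / 10% | 93 | 3 | 3 | 5.0 |
| 10% / 5% | 93 | 16 | 34 | 5.0 |
| 15% / 5% | 93 | 51 | 84 | 4.9 |
| 20% / 5% | 93 | 80 | 99 | 5.3 |
| 20% / 10% | 93 | 35 | 67 | 4.8 |
| 25% / 10% | 93 | 64 | 93 | 4.9 |
| 10% / 10% | 296 | 4 | 4 | 5.6 |
| 10% / 5% | 296 | 55 | 86 | 4.9 |
| 15% / 5% | 296 | 97 | 100 | 4.6 |
| 20% / 5% | 296 | 100 | 100 | 5.7 |
| 20% / 10% | 296 | 88 | 100 | 4.7 |
| 25% / 10% | 296 | 99 | 100 | 5.0 |

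Running the test in each arm and contrasting the p-values does not help. With identical arms and unequal moves, one arm was significant and the other was not in 28% to 49% of trials at 93 per arm.

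**The case against.** The strongest reply is that the valid tools are already in the plan. The general methods text provides chi-squared and Fisher's exact tests for categorical outcomes and logistic regression for binary ones, and it presents Table 3 as a summary. On that reading this is a mismatch between table and text. The proposed mechanism, more nodes removed, also has its own row with a valid between-arm analysis. Both observations are true. But Table 3 assigns none of the valid categorical tests to staging, the general text itself lists McNemar's test as an alternative, and node count is not stage.

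A second reply is that no section says the arms would be pooled, and that within one arm the 20%/10% example gives p about 0.06. This is fair as to size: the pooled figures are the more extreme case. It does not change the conclusion, since the within-arm test also rejects far above 5% with identical arms whenever up- and downstaging differ (16% to 80% at 93 per arm). When they are equal the test keeps its level, but it still says nothing about RTS against VATS.

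Third, Bowker's extension handles more than two stage levels, and an analysis plan not shown could dichotomise stage. That weakens the point about a binary variable. Neither step brings the arm into a within-patient test.

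Finally, staging is one of seven short-term clinical rows, drives neither sample size, and has no stated priority. That limits the reach of the error.

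**Conclusion.** The point holds. The only test Table 3 assigns to pathological staging cannot address the hypothesis in the same row. This follows from the design and the form of the statistic, and it does not depend on any assumed rate.

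The size of the possible error does depend on assumptions, because the article gives no upstaging or downstaging rates. With identical arms of 93 and unequal rates, false signals ranged from 16% to 80% within an arm and from 34% to 99% pooled; at 296 per arm they were higher. With equal rates there is no inflation, only a test of the wrong question.

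The damage is confined to one secondary outcome. The primary EQ-5D-5L analysis, both sample sizes, and the cost and survival analyses are untouched. It should still be corrected, since the row is wrong as written and the correction costs almost nothing.

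**What to change.** - In the Pathological Staging row of Table 3, define a per-patient endpoint, for example upstaged from clinical to pathological stage (yes/no), or nodal upstaging.
- Compare it between arms by chi-squared or Fisher's exact test, with logistic regression for the adjusted analysis. Clinical stage and surgeon (the stratification factor) are natural covariates. Report the effect with a 95% confidence interval. The relative risk or odds ratio already planned is sufficient; a risk difference is optional.
- Remove McNemar's test from the general list of group comparisons. If it is kept, label it a within-arm description of agreement between clinical and pathological stage, with no inference about treatment.
- Align the staging sentence under Secondary analysis with the new endpoint.

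The cost is a change of wording. Clinical and pathological stage are already collected, and the replacement methods are already in the plan. Trial status reports Phase A recruitment and follow-up as almost complete, so the change should be made and dated before the Phase A analysis, while the analyst is still blinded to allocation.

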#### Secondary outcome in Phase B

Differences in QALY will require a higher number of measurements to be detected. Overall survival at 5-years will also require a larger sample size over a longer period of observation. These secondary outcomes of interest require the trial to be repowered so that they can be adequately powered. Based on a hypothesized 10% 5-year survival difference between the control arm and the experimental arm, the estimated sample sizes for two-sample comparison of survivor functions using the Log-rank test Freedman method with 80% power at a level of significance of 0.05 is 592 patients, with 296 patients per arm. A drop-out rate is not factored into this analysis since the Freedman method of censoring was employed, accounting for loss of patients over time. Also, an assumption for Stage I patients was made during this sample size calculation, since the majority of patients who are operated on are Stage I. Also, this calculation is not a non-inferiority design. This larger, sufficient sample size will allow comparison of difference in overall cost-effectiveness and survival.

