#### Baseline data collection

Baseline data including demographics (e.g., age, BMI, gender), medical history (e.g., smoking, alcohol use, comorbidities, analgesia consumption, pain, previous thoracic surgery, previous cancer), tumour characteristics (e.g., clinical stage, histology), and physiology (e.g., pulmonary function) will be collected. In addition, participants will be asked to complete the Trial Health Questionnaire and they will be provided with a Study Diary.

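### The log-rank test that sizes Phase B carries no stratification by clinical stage, which gives up a modest amount of precision that a recorded baseline variable could recover

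*Protocol article*

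**What the plan says.** The section on statistical methods for primary and secondary outcomes gives the survival analysis in two sentences: "Survival will be compared using the Kaplan-Meier method and cox proportional hazard models. Survival curves will be compared using the Log-rank test". The overall survival row of Table 3 repeats this: "Kaplan-Meier method and cox proportional hazard models. Survival curves will be compared using the Log-rank test". Neither place names a stratification factor or a covariate. The same section does describe adjustment for other outcome types: "For adjusted analyses, multivariable logistic regression analyses will be used for binary outcomes and multivariable linear regression for continuous outcomes".

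The Phase B sample size section starts from this target: "Based on a hypothesized 10% 5-year survival difference between the control arm and the experimental arm". It reaches 592 patients (296 per arm) by Freedman's method for the log-rank test, at 80% power and a 0.05 significance level, and it assumes stage I patients because they are the majority.

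Three other sections bear on stage. The inclusion criteria admit clinical stages I, II and IIIa. Under sequence generation, "Randomization was stratified by surgeon", with no mention of stage. Baseline data include "tumour characteristics (e.g., clinical stage, histology" among the items recorded.

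**The concern.** The eligible stages are likely to carry different risks of death, and the sample size section treats stage as relevant to survival by assuming stage I. Nothing in the randomisation balances stage between arms beyond chance. A log-rank test without strata pools patients with different hazards into one risk set. When stage is prognostic, this has two consequences. The test gives up some power against a treatment effect that acts within stages. The observed result also moves with whatever stage imbalance the single randomisation happens to produce.

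Phase B is planned at 80% power with no addition for drop-out, so there is little slack. The variable that would recover the loss is already collected before surgery.

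**Working it through.** **1. Reproduce 592.** The control rate is not stated, so control survival was scanned with the experimental arm 10 points higher (two-sided 0.05, 80% power, 1:1). At 70% versus 80%:

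- HR = ln(0.80)/ln(0.70) = 0.626
- Deaths (Freedman) = (1.960 + 0.842)² × [(1 + 0.626)/(1 − 0.626)]² = 148
- N = 2 × 148/(2 − 0.70 − 0.80) = 592

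This matches the plan exactly. It is a calculation for one homogeneous population, with no stage term.

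**2. Size of a chance imbalance.** The SD of the between-arm difference in the stage II–IIIa share p is √[2p(1 − p)/296].

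- p = 0.10: √(0.18/296) = 2.5 points
- p = 0.30: √(0.42/296) = 3.8 points
- p = 0.40: √(0.48/296) = 4.0 points

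For scale, take p = 0.30 and assume 5-year survival of 80% in stage I and 48% in stages II–IIIa combined. A 2-SD imbalance (7.5 points) then shifts the survival difference by 0.075 × (0.80 − 0.48) = 2.4 points. The standard error of that difference is √[(0.7 × 0.3 + 0.8 × 0.2)/296] = 3.5 points.

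**3. Power with and without stage strata.** Simulation with 296 per arm, exponential survival, censoring at 5 years, the same hazard ratio in every stage, and 8,000 to 10,000 trials per row. Stage mixes and stage-specific survival are assumptions.

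Setting A: HR 0.626 within every stage.

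| Stage I/II/IIIa (%) | Control 5-year survival (%) | Plain | Stratified |
|---|---|---|---|
| 100/0/0 | 70 in stage I | 81% | 81% |
| 90/7/3 | 70/50/35 | 83.0% | 83.8% |
| 80/15/5 | 70/50/35 | 85.4% | 86.8% |
| 70/20/10 | 70/50/35 | 87.1% | 88.7% |
| 60/25/15 | 70/50/35 | 89.3% | 91.4% |
| 70/20/10 | 70/40/25 | 87.5% | 91.1% |

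Setting B: overall 5-year difference held at 10 points.

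| Stage I/II/IIIa (%) | Control 5-year survival (%) | Plain | Stratified |
|---|---|---|---|
| 90/7/3 | 68/50/35 | 77.6% | 78.1% |
| 80/15/5 | 70/50/35 | 76.2% | 78.2% |
| 70/20/10 | 75/50/35 | 77.3% | 81.2% |
| 60/25/15 | 75/50/30 | 75.3% | 80.9% |

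The gain runs from 0.5 points (78.1 − 77.6) to 5.6 points (80.9 − 75.3). Setting A has more than 148 deaths in the mixed rows, so both tests exceed 80% there. In setting B overall control survival is 62 to 66%, which is part of why the plain test falls below 80%.

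**4. Validity and conditional behaviour.** With no treatment effect, both tests reject about 5% of the time averaged over randomisations. In setting A, chance imbalance in the stage I share explains about 2 to 11% of the variance of the plain statistic and none of the stratified one. A 2-SD imbalance moves the plain hazard ratio by about 4 to 8%. If an 8-point stage I imbalance is imposed with no treatment effect, the plain test rejects 7.0 to 8.0% of the time and the stratified test 4.3 to 5.4%. Eight points is about 2 SD when 60 to 70% are stage I, but more than 3 SD when 90% are.

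**The case against.** The strongest reply is that this is a journal article whose analysis plan is not shown, and that strata and Cox covariates are details normally placed there. That reply stands for the Cox models. They are named with covariates open, so a reader who infers that the whole survival analysis ignores stage goes further than the text. It stands less well for the log-rank test. That test is named twice without strata and is the basis of the sample size, so an analysis plan that stratified it would change what the article states.

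A second reply is that chance imbalance under randomisation is random error already covered by the test. This is correct. A reader might infer confounding or a biased design, but the type I error near 5% rules that out. What remains is that the one realised trial can be imbalanced, and adjusting only after seeing the imbalance would be post hoc.

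A third reply is that the gain depends on assumptions. This is also correct. If nearly all patients are stage I, as the sample size section leans towards, the gain is under one point. A gain as large as 82% to 90% appears only with a 60/25/15 mix and a steep assumed stage effect (control survival about 87/54/30%), which the documents do not support.

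Finally, one might fear that survival will be adjusted for pathological stage, which the trial expects surgery type to affect. No section proposes this. It is only a reason to name clinical stage explicitly.

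**Conclusion.** The point holds as a modest loss of precision in a secondary outcome, not as an error of validity. The stated log-rank test leaves out a baseline variable that the trial already records and does not balance by design. Stratifying by it gains roughly 0.5 to 6 points of power at 592 patients and removes the influence of a chance stage imbalance on the result. The direction was the same in every stage-mixed scenario. The size rests on assumed stage mixes (60 to 90% stage I), assumed stage-specific survival, exponential survival times and a common hazard ratio across stages. The documents do not establish that the plain test would miss its 80% target: in the simulations it lies above or below that figure depending on the assumptions.

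**What to change.** In the statistical methods section and in the overall survival row of Table 3, name as the main overall survival test a log-rank test stratified by clinical stage at randomisation (I, II, IIIa), with the hazard ratio from a Cox model stratified the same way. State that clinical and not pathological stage is used. Keep the unstratified log-rank test and the Kaplan-Meier 5-year difference as supportive results.

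The change needs no extra patients or visits, and no data beyond what any log-rank test requires. On that last point, the follow-up section says that only alive-or-not status is collected at five years. Either form of the test needs dates of death or censoring, so that statement should be reconciled separately.

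The one real cost is that the hazard ratio becomes conditional on stage, whereas the Phase B target is a marginal 10-point difference. The marginal 5-year difference must therefore be reported alongside it. Recruitment is expected to run to the end of 2031 and no interim analysis is planned, so the change can be made before survival is analysed.
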